#### Sample Size Calculation

The sample size was calculated using Granmo calculator v.7.12, based on a three-arm parallel-group design and ANOVA for means (SDs). The primary assumption was that the minimum clinically important difference (MCID) according to the VAS score is 13.5% (0.135). This value was derived from a previous NCNP study [27] and represents the minimum pain reduction considered meaningful by patients and clinicians.

The statistical parameters are as follows: alpha risk (type I error): 5% (two-sided); beta risk (type II error): 10% (power=90%); SD of mean VAS scores: estimated as 12% (0.12) based on a pilot study ([name], unpublished data, 2022).

The initial sample size was calculated as 45 participants (n=15, 33.3%, per group) to detect the specified MCID under ideal conditions (no dropouts). To make adjustments for follow-up losses, we anticipated an 8% dropout rate (based on similar rehabilitation trials [8]), so the final sample size was increased to 69 participants (n=23, 33.3%, per group) to ensure at least 20 evaluable patients per group after attrition.

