The aim of this study is to compare the therapeutic effects of tuina, PNF, and their combination in the treatment of NCNP and whether the combination therapy of PNF and tuina has superior efficacy compared to either therapy alone in order to provide more clinical evidence for the treatment of NCNP. Against this backdrop, this study aims to address three critical research questions:

Does the PNF technique demonstrate superior efficacy compared to tuina in reducing pain and improving functional disability?Does the combination of PNF and tuina yield better outcomes than either monotherapy alone?Are there significant differences in cervical joint mobility and muscle physical properties (eg, stiffness, elasticity) across the three treatment groups?

The specific objectives are to (1) compare the short-term (end of intervention) and long-term (4-week follow-up) efficacy of PNF, tuina, and their combination in reducing pain (VAS score) and functional disability (NDI); (2) evaluate their effects on cervical active joint mobility and muscle physical properties; and (3) assess the safety and tolerability of all interventions. Guided by these objectives, the primary hypothesis is that the PNF-tuina combination will achieve greater reductions in pain and disability than monotherapies, while the secondary hypothesis posits that PNF will outperform tuina in improving cervical biomechanics. All interventions are hypothesized to be safe, with low rates of adverse events (AEs).

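### The sample-size derivation does not reproduce: 15 per group gives roughly 70-88% power rather than 90%, and an 8% loss turns 45 into 49-51, not 69

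*Protocol article*

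**What the plan says.** The Sample Size Calculation section of the protocol article describes a three-arm ANOVA on means. It uses a minimum important VAS difference of 13.5% (0.135), a two-sided type I error of 5%, power of 90%, and "SD of mean VAS scores: estimated as 12% (0.12) based on a pilot study". From these it reports: "The initial sample size was calculated as 45 participants (n=15, 33.3%, per group) to detect the specified MCID under ideal conditions", with no dropouts. It then anticipates 8% dropout, "so the final sample size was increased to 69 participants (n=23, 33.3%, per group) to ensure at least 20 evaluable patients per group after attrition".

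The section does not say how the three means are assumed to lie relative to one another, or why the evaluable target rises from 15 to 20 per group.

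Three other places bear on the point:
- The Introduction says that "the primary hypothesis is that the PNF-tuina combination will achieve greater reductions in pain and disability than monotherapies".
- Statistical Analysis names Bonferroni for post hoc comparisons.
- Study Design gives a total of 102 patients. Randomization (23 per group), Results and Limitations all use 69.

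**The concern.** A sample-size statement should let a reader go from inputs to total. Here both links fail. The first says 15 evaluable per group is enough for 90% power. The second presents the rise from 45 to 69 as an allowance for 8% loss, which is far too small to explain it.

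The stake is how the figures will be read. Someone who trusts the text will take 15 per group as the number that carries 90%, and 69 as that number plus a margin. The 90% may also be read as the chance of supporting the primary hypothesis. It belongs to a different question: whether the three VAS means differ at all.

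**Working it through.** **Inputs** (Sample Size Calculation): difference 0.135, SD 0.12, two-sided alpha 0.05, power 90%, three equal groups, ANOVA. Standardised difference d = 0.135/0.12 = 1.125. The pattern of means is not stated, so I bracket it.

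**Step 1: power at 15 per group, ANOVA.** The effect size is f² = Σ(mean − grand mean)²/(3·SD²), the noncentrality is λ = 3n·f², and the critical F(2, 42) is 3.22.
- Third mean midway (0, 0.0675, 0.135): f² = d²/6 = 0.211, λ = 45 × 0.211 = 9.49, power **76.2%**.
- Two means equal (0, 0, 0.135): f² = 2d²/9 = 0.281, λ = 45 × 0.281 = 12.66, power **87.7%**.

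With a range of 0.135 between the extreme means, these are the smallest and largest f that three equal groups can have, so the ANOVA answer lies between them.

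**Step 2: power at 15 per group, pairwise t.** Noncentrality d√(n/2) = 1.125 × √7.5 = 3.08, on 28 df.
- Alpha 0.05: **84.5%** (normal approximation 86.9%).
- Alpha 0.05/3: **70.1%** (normal approximation 75.4%).

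**Step 3: what would reproduce 15?** Two readings do, and neither is valid here.
- A one-sided 5% t-test gives 91.3%, but the section says two-sided.
- An ANOVA with f = d/2 = 0.563 gives 91.3%, but the largest attainable f is √0.281 = 0.530.

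**Step 4: group size for 90% with the ANOVA.**
- Two arms equal: 17 per group (91.8%; 16 gives 89.9%).
- Third arm midway: 22 per group (91.4%; 21 gives 89.95%).

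**Step 5: dropout** (no assumption about means needed).
- 45/0.92 = 48.9, so 49. By arm, 15/0.92 = 16.3, so 17 per group, or 51.
- From 45 to 69, the implied loss is 1 − 45/69 = 34.8%.
- Starting from 20 evaluable: 20/0.92 = 21.7, so 22 per group, or 66.
- 23 per group with 8% loss leaves 23 × 0.92 = 21.2.

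**Step 6: what 69 delivers.** The last two columns are the power for the combination to beat both monotherapies on VAS. They come from simulation, with the monotherapies equal and the SD pooled over the three groups.

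| Evaluable per group | ANOVA, midway | ANOVA, two equal | Beats both, Bonferroni (3 pairs) | Beats both, each at .05 |
|---|---|---|---|---|
| 15 | 76% | 88% | 59% | 76% |
| 20 | 88% | 96% | 77% | 89% |
| 21 | 90% | 97% | 80% | 91% |
| 23 | 93% | 98% | 85% | 94% |

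The last two columns share the two-equal pattern, so they should be compared with the third column and not with the second.

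**The case against.** The best defence is that the final size is adequate and only its explanation is faulty. That stands. The same sentence that reaches 69 sets a floor of 20 evaluable per group, and at 20 the ANOVA has 88-96%. If the monotherapies are equal, the pattern closest to the primary hypothesis, 15 per group misses 90% by only about 2 points. Quoting 76% as the single answer would therefore be unfair, because it is the least favourable ANOVA pattern and the protocol does not state it. A baseline-adjusted analysis could also raise power at 15 above 90% in the two-equal case (90.7% with an assumed baseline correlation of 0.3). But the section describes an ANOVA with SD 0.12 and gives no correlation, so this cannot be its derivation.

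Some stronger readings are tempting, and the document does not support them:
- **The 8% loss contradicts the floor of 20.** It does not: 21 remain, which is at least 20. The gap is that the move from 15 to 20 is unexplained.
- **The intended figure was 63 (21 per group), since 63/0.92 = 68.5.** That fits 69, but it is a guess. Power at 21 with midway means is 89.95%, so 22 are strictly needed, and 66/0.92 = 71.7 gives 72. With equal monotherapies 17 suffice.
- **Power for winning on both VAS and NDI is lower still.** No NDI difference, SD or correlation with VAS is given, so no figure can be put on it.

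**Conclusion.** The derivation is wrong as written. On the stated inputs, power at 15 per group is about 70-88%, depending on the pattern of means and the adjustment, and no valid two-sided calculation from those inputs reaches 90%. The dropout error needs no assumption about means: 8% gives 49-51, and 69 would need a 35% loss.

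A reader might infer that the trial is underpowered at 69. The figures do not show that for the overall ANOVA of VAS. After 8% loss it has about 90% with midway means and 97% with two arms equal. What the 90% does not cover is the primary hypothesis. On VAS alone, with equal monotherapies and Bonferroni over three pairs, the power to beat both is about 77% at 20, 80% at 21 and 85% at 23 per group. It is about 89-91% at 20-21 if each contrast is tested at .05. All of this takes the protocol's 0.135 and 0.12 at face value.

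**What to change.** In Sample Size Calculation:
1. State the assumed pattern of the three means, rerun the calculation, and replace the initial 45 (15 per group) by the result. On these inputs that is 17 per group if the monotherapies are equal, or 22 if the third arm is midway.
2. Stop presenting 69 as 45 plus 8%. Justify it by the power at the expected evaluable number (20-21 per group), and say why 20 is the floor.
3. Say that the 90% refers to the three-group ANOVA of VAS, and give beside it the power for the combination to beat both monotherapies on VAS, with the assumption and the adjustment named.
4. Reconcile 69 with the 102 in Study Design, so that one total stands throughout.

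The cost is rewording one section and correcting one total. No additional patients are needed on this ground, and conduct and analysis do not change. The power stated for the primary hypothesis will look less favourable than 90% if Bonferroni is kept.

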#### Quality Control

With the management of the steering committee, quality control will be conducted during the processing of the trial. Professional trial and regular monitoring training sessions will be conducted before the researchers participate in the trial, which will ensure consistency of the methods. The steering committee and ethics committee will be informed if the study protocol is modified or corrected.

## Results

As of the data cutoff date (May 26, 2025), 43 participants were enrolled and randomly assigned to the three treatment groups (PNF group: n=14, 32.6%; tuina group: n=15, 34.9%; combined group: n=14, 32.5%), with recruitment initiated on April 1, 2025, via hospital outpatient clinics (n=45, 65.2%) and online posting (n=24, 34.8%). All enrolled participants have initiated treatment, with an average adherence rate of 92% (measured using session attendance records), and no withdrawals have occurred due to AEs or treatment dissatisfaction. The short-term follow-up (end of intervention) for the first cohort was completed on July 30, 2025, with long-term follow-up (1 month postintervention) to be completed by August 31, 2025. The final analysis is projected to include data of all 69 participants by October 2025, with primary results planned for publication in December 2025.

## Discussion

### Summary

NCNP is a widespread musculoskeletal disorder associated with significant functional impairment and a huge economic burden, aligning with previous reports highlighting its impact on activities of daily living and work productivity. Our RCT aims to evaluate the efficacy of PNF, tuina, and their combination, two interventions with distinct theoretical foundations, in treating NCNP. Studies have demonstrated that tuina reduces neck pain by enhancing blood circulation and releasing myofascial tension [28], while PNF is hypothesized to improve neuromuscular control and joint mobility through proprioceptive stimulation [29]. However, this is among the first RCTs to directly compare these modalities head-to-head and assess their synergistic effects. Notably, our preliminary results (interim analysis) suggest that the combination group achieved a 42% reduction in VAS scores at 4 weeks, significantly greater than the 28% and 31% reductions in the tuina and PNF groups, respectively. The results of this study are similar to those of a systematic review on adjunctive therapies for chronic pain [30], which reported that the combination of manipulative therapy and exercise results in better outcomes. However, this contrasts with a study by Qi et al [31], who found no increased effect of PNF in combination with acupuncture, which may be due to differences in the duration of the intervention (2 months compared to our 4-week regimen) or patient selection criteria.

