**Methods:**

The parallel, double-blind, three-arm clinical randomized controlled trial (RCT) is being conducted at the Beijing University of Chinese Medicine and its affiliated hospitals. Patients will be recruited and randomly assigned to a PNF group, a tuina group, and a combined (PNF+tuina) group in a 1:1:1 ratio. The PNF intervention (PNF stretching and PNF plyometrics) will last for 30 minutes each session. Tuina therapy will also last for 30 minutes each session. The combined group will receive 30 minutes of PNF, followed by 30 minutes of tuina therapy. Participants will receive 4 weeks of treatment, thrice a week, for a total of 12 treatments. Visual Analogue Scale (VAS) and Neck Disability Index (NDI) scores will be used as primary outcome measures. Cervical active joint mobility measured with the MicroFET3 Portable Muscle Strength Test and Joint Mobility Meter and muscle physical properties tested with the Myoton Muscle Tester will be used as secondary outcome measures. Data will be analyzed at baseline, at the end of the intervention, and during the 4 weeks of follow-up using repeated measures ANOVA. The significance level will be 5%.

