### Blinding

Outcome assessors, data managers, and the statistician will be blinded in this trial and will not share study information with each other. To preserve masking, only the massage therapists will have access to treatment allocation. The patients will not know the group to which they belong before the intervention. The sequence of randomization will be hidden from both evaluators and patients, and this sequence will be kept by the main researcher throughout the study and will not be available to the rest of the participants involved in the trial.

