#### Statistical Analysis

The intention-to-treat principle will be followed in the primary data analysis with IBM SPSS Statistics for Windows version 27.0 software by statisticians who are blinded to the group allocation. Baseline characteristics will be expressed with descriptive statistics for the groups as the mean (SD). The Kolmogorov-Smirnov test with Lilliefors correction will be performed to analyze all quantitative variables to determine whether they follow a normal distribution. Parametric statistics (Tukey test) or nonparametric statistics (Wilcoxon rank-sum test) will be used for the within- and between-group analyses in accordance with the results of homogeneity and normality analyses. When initial homogeneity and normality of data distribution are found, repeated measures ANOVA and ANOVA with Bonferroni post hoc statistics will be used for within- and between-group analysis. The Friedman test and the Kruskal-Wallis test will be performed when initial homogeneity but not normality of data distribution is found. If initial homogeneity is not found, a linear mixed model will be adjusted for the baseline value. AEs in each group will be documented as percentages for safety assessments using the chi-square test or the Fisher exact test. Statistical significance is defined as *P*<.05, and 95% CIs will be reported.

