### Conclusion

This study provides preliminary evidence that the combination of PNF and tuina may offer superior short-term pain relief compared to monotherapies for NCNP. Although rigorous replication in larger, more diverse populations is needed, these findings justify further investment in integrative rehabilitation strategies for this challenging condition.

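### An interim by-arm VAS comparison is reported as significant and used for a superiority conclusion during follow-up, although the Methods describe no efficacy look and leave the level at 5%

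*Protocol article*

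**What the plan says.** The Discussion (Summary) labels the result itself: "our preliminary results (interim analysis) suggest that the combination group" did better. It then gives VAS reductions of 42% for the combination, 28% for tuina and 31% for PNF, and calls the difference significant: "the combination group achieved a 42% reduction in VAS scores at 4 weeks, significantly greater than the 28% and 31% reductions". It gives no number of patients, data date, standard deviation, confidence interval, P value or test. The Conclusion adds: "This study provides preliminary evidence that the combination of PNF and tuina may offer superior short-term pain relief compared to monotherapies for NCNP".

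The rest of the article describes a trial with one efficacy analysis, at the end:

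- Statistical Analysis: "Statistical significance is defined as" P<.05, with no interim look and no adjustment for one. The abstract gives the same 5% level, and Sample Size Calculation lists "alpha risk (type I error): 5% (two-sided").
- Ethical Considerations: the monitoring board oversees participant safety and reviews adverse event reports. No efficacy review is mentioned.
- Blinding: "Outcome assessors, data managers, and the statistician will be blinded in this trial".
- Results: "The final analysis is projected to include data of all 69 participants by October 2025". One-month follow-up of the first cohort was to run to 31 August 2025, after the publication date of 14 August 2025.

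**The concern.** The reported comparison is the trial's primary hypothesis, that the combination beats each monotherapy on pain. A significance statement and a conclusion about it already stand in print, and the same hypothesis will be tested again at the full 5% once all patients are in. Two things are at stake.

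The first is the false-positive rate of the superiority claim, if both results are allowed to carry it.

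The second is the integrity of the data still to come. VAS and NDI are self-reported. A published statement that one named arm is ahead can reach participants, therapists and assessors while week-8 scores, and possibly some week-4 scores, are outstanding. No later analysis can remove expectation that has entered a self-report.

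**Working it through.** **The plan's own figure.** One two-sided test at P<.05, done once at the end, has a type I error of 5% for that comparison. This agrees with the level in the abstract, Statistical Analysis and Sample Size Calculation.

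**Two looks at an unadjusted 5%.** Let t be the share of the final information present at the interim. If the combination is no better, the interim and final statistics for the same contrast are approximately bivariate normal with correlation √t. The chance that at least one is significant is

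1 − P(|Z₁| < 1.96 and |Z₂| < 1.96), with corr(Z₁, Z₂) = √t.

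**Inputs.** The final sample is 69 (Sample Size Calculation, Results). By 26 May 2025, 43 had been randomised (14 PNF, 15 tuina, 14 combined; Results). The number in the interim analysis is not stated, so t has to be assumed:

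- All 43 included: t = 43/69 = 0.62.
- Only those who could have reached week 4 by 26 May: recruitment began on 1 April, 55 days earlier, so they had to enter within the first 27 days. With even accrual (assumed) that is 43 × 27/55 ≈ 21, and t = 21/69 ≈ 0.30.
- Data up to the time of publication: at the same pace, patient 69 enters after 69 × 55/43 ≈ 88 days, about 28 June, and reaches week 4 about 26 July. Then t for week-4 VAS could be close to 1.

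| t | √t | False claim at either look |
|---|---|---|
| 0.30 | 0.55 | 8.9% |
| 0.50 | 0.71 | 8.3% |
| 0.62 (43/69) | 0.79 | 7.9% |
| 0.75 | 0.87 | 7.3% |
| 0.90 | 0.95 | 6.5% |

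As t approaches 1 the two tests become the same test and the figure returns to 5%.

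**Check by simulation.** Three arms with no true difference, 14 per arm at the interim and 23 per arm at the end, 100,000 trials:

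| Test | Final only | Either look |
|---|---|---|
| One pairwise contrast | 4.9% | 7.9% |
| Overall F test | 4.9% | 8.0% |
| Any Bonferroni-adjusted pair | 4.3% | 7.0% |

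The final-only column matters as much as the other: when the interim result supports no claim, the final test does not exceed its nominal level.

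**Disclosure.** No arithmetic applies. The Blinding section masks assessors, data managers and the statistician, yet the Discussion prints results by named arm before the follow-up dates given in Results have passed. The article does not say who linked outcomes to arms, or when.

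**The case against.** The best defence is that nothing ties the look to a decision. Results projects a final analysis of all 69, and the Discussion and Conclusion use hedged wording (preliminary, may). If the trial runs to 69 whatever the interim showed, and only the final test is confirmatory, that test keeps its 5%. This stands, and it is why the inflation is stated conditionally. It does not excuse the significance wording or the conclusion, because these already use the interim result as evidence of superiority.

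Other parts of the defence also stand. The 26 May date is the cut-off for the enrolment count and need not be that of the interim data, so 43/69 is one assumption among several. The Blinding section masks patients to group only before the intervention and leaves the sequence with the main researcher, so a by-arm summary does not prove that assessors were unblinded.

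A reader might infer more than the documents support:

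- *That the look was unplanned.* The article condenses a fuller protocol, and an analysis plan may exist. What can be said is that the Methods describe no such look.
- *That the significance claim cannot be true.* This turns on an undefined unit. Taking the planning SD of 12% as 1.2 VAS points, with an assumed mean baseline of 5 and 14 to 15 per arm, gives P of about .12 (against tuina) and .23 (against PNF). Taking it as the SD of the percentage reductions gives .003 and .020. The documents do not settle which applies.
- *That the trial may stop on these results.* Study Design gives 102 patients and Sample Size Calculation gives 69, but no text links either figure to the interim result.
- *That an alpha-spending boundary would repair it.* A boundary chosen after the result is published is post hoc, and it depends on the unknown fraction: O'Brien-Fleming-type spending gives an interim level of .013 at 0.62 and about .0004 at 21/69.

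**Conclusion.** The point holds in a limited form. The article reports an efficacy comparison that its Methods do not describe, calls it significant, and concludes from it while primary outcome data were still being collected.

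If that result and the final test may both support superiority, the chance of a false claim is about 6.5% to 9% for information fractions from 0.9 to 0.3, and 7.9% if all 43 patients were in the look. This assumes the same VAS contrast, each time at an unadjusted two-sided 5%. The fraction is an assumption throughout, and the excess disappears as it nears 1. If only the final test counts, the rate is 5%.

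The expectation effect on the remaining self-reports is plausible but cannot be quantified from the documents.

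**What to change.** 1. Discussion (Summary) and Conclusion: remove the by-arm percentages, the statement of significance and the superiority conclusion.
2. Statistical Analysis: state that the interim look had no decision role, does not change the sample size target and supports no efficacy claim, so that the analysis of the full sample is the only confirmatory test, at the stated 5%. Only the sponsor can confirm that the look had no decision role; if it did have one, the section must say what it was.
3. State how many patients per arm were in the look, its data date, and who saw outcomes by arm.
4. Release no further by-arm results until the last follow-up visit.

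The cost is text only: no change to sample size, final significance level or power. Correcting the article does not undo the disclosure already made, which is why item 3 is needed for readers of the final report to judge it.
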